## Discussion

The societal relevance of this study consists of substantial personal, social and financial savings if guideline-based care leads to faster and sustainable RTW of workers with CMD. Since previous studies indicate that guideline adherence of OPs can lead to a shortened sick leave duration [6,12,13], the training described in this study aims to improve the OPs’ guideline adherence. Therefore, the present study evaluates the effect of guideline-based care on full RTW of workers with CMD.

### Strengths and limitations

A strength of this study is the collaboration with one of the largest OHS in the Netherlands; this provides a diversity of companies covering many sectors, yielding a heterogeneous population which allows to generalise the results to a larger working population. Furthermore, because the innovative training is spread over one year, OPs can explore the barriers, apply solutions, evaluate their experiences, and adapt the solutions until they are useful in daily practice. This is in contrast to earlier studies which evaluated short term training only. Another strength is that the participating workers are selected by the registration system of the OHS and not by OPs; this may prevent selection bias from the individual OPs. Finally, the workers are blinded for randomisation to the intervention or control group to prevent performance bias.

Limitations: although the extent of guideline adherence by OPs will be measured by auditing the medical records of workers, there is a risk that this will not provide accurate information on guideline adherence: e.g. OPs might not document everything that occurred during the counselling. Another limitation might be that 232 workers are needed and followed during one year, whereas earlier studies had a problem recruiting sufficient workers. However, collaborating with one of the largest OHS in the Netherlands should ensure sufficient sick-listed workers, i.e. 60 OPs need to counsel 3-4 workers each to reach the total of 232 workers.

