### Intervention

#### Intervention/guideline-based care

The Dutch guideline ‘The management of mental health problems of workers by occupational physicians’ promotes an activating approach of the OP as case and care manager to enhance the problem-solving capacity of the workers to achieve RTW. The guideline is based on cognitive behavioural principles to enhance the problem-solving capacity of workers in relation to their work environment, and process-based evaluation.

The guideline consists of four consecutive steps:

1) Problem orientation and Diagnosis: an early involvement of the OP is promoted (first assessment and start of counselling about 2 weeks after the worker reported sick). A simplified classification of mental health problems is introduced in four categories: i) Stress-related complaints, ii) depression, iii) anxiety disorder, and iv) other psychiatric disorders. Furthermore, problem inventory should focus on factors related to the worker and their work environment and the interaction between these two.

2) Intervention/Treatment: the OP acts as case manager by monitoring and evaluating the process of recovery (process-based evaluation). When recovery stagnates OPs should intervene by acting as care manager by using cognitive behavioural techniques to enhance the problem-solving capacity of the worker, providing the worker and work environment with information/advice on the recovery and the RTW process, contact the general practitioner when problems remain the same or increase, and refer the worker to a specialised intervention when necessary. In addition, the OP should advise the work environment (e.g. supervisors, managers, human resource managers) how to support the worker and enhance the recovery and RTW process.

3) Relapse prevention: Integration of relapse prevention from the first contact with the worker by enhancing the problem-solving capacity of the worker.

4) Evaluation: During follow-up meetings evaluation of the recovery process includes the perspectives of the worker, supervisor, and other involved professionals. Follow-up meetings with the worker should take place every 3 weeks during the first 3 months, and then every 6 weeks thereafter. The supervisor or work environment should be contacted once a month. Follow-up contacts with the general practitioner or other professionals should take place when the recovery process stagnates or when there is doubt about the diagnosis or treatment.

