#### Content of the training

OPs participating in the study and allocated to the intervention group received training in the guideline before the start of the study. This training was specifically designed for the purpose of this study and consisted of 8 meetings within 12 months. Each meeting took 2 h and was provided in groups of 4-6 OPs under the guidance of a trainer. The aim of the training was to enhance guideline adherence of the participating OPs by focussing on barriers that prevent OPs from using the guideline and finding solutions to overcome these barriers. This is considered to be a successful strategy for the implementation of guidelines [15,16].

During the 8 meetings the (key) recommendations within each consecutive step of the guideline were discussed. These discussions first focussed on barriers that would hinder OPs from using the specific recommendation in practice. The analysis of barriers was structured and based on an existing framework of barriers [17]. According to this framework guideline adherence can be affected by three main categories: 1) knowledge-related barriers (lack of awareness and lack of familiarity), 2) attitude-related barriers (lack of agreement, lack of self-efficacy, lack of outcome expectancy and lack of motivation/inertia of previous practice) and 3) external barriers that hinder physicians to apply the guideline in practice (guideline factors, environmental factors and patient factors). Second, the OPs in the group were invited to suggest solutions to address the perceived barriers taking into account the context of their daily practice. Third, the OPs drew up an action plan of how to implement these solutions in their daily practice, and agreed on learning objectives and ‘homework’ assignments. Between the meetings (a period of about 6 weeks) the OPs practiced the suggested solutions to experience if and how these would help to apply the guideline recommendations. During the next meeting the experiences of the OPs were evaluated and, when necessary, the solutions were adjusted to what the OPs had experienced in practice. This cycle of plan-do-check-act was repeated in each meeting for all the recommendations stated in the guideline.

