### Recruitment of participants

The study is conducted in the southern part of the Netherlands. The workers eligible for this study are on sick leave due to CMD diagnosed by the OP, counselled by an OP participating in the study, have had a first meeting with the OP, and are aged 18–65 years. From all eligible workers data on sick leave and RTW will be extracted from the registration system of the OHS anonymously.

Workers eligible for the data collection by means of the questionnaires work at one of the ± 320 companies served by this collaborating OHS that gave permission to invite their workers. The companies vary in size and serve different sectors. These workers are selected from the registration system of the OHS after their first consultation with the OP. They are sent an invitation letter from the OHS, as well as written information about the study. Workers who do not want to be contacted further can indicate this on a reply card. All eligible participants are contacted for additional information, and to check the inclusion and exclusion criteria. If the worker is willing to participate in the study and meets all the selection criteria, an informed consent and the baseline questionnaire will be sent to the worker.

Inclusion criteria for this study are: 1) CMD is the primary reason for sick leave diagnosed by an OP according to the Dutch Classification of Diseases (CAS) which is based on the ICD-10, 2) on current sick leave when selected from the registration system of the OHS after the first meeting with the OP, and 3) adequate command of the Dutch language. Exclusion criteria are: being suicidal, and a physical problem being the primary reason for sick leave at the time of study inclusion.

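### Selecting workers through the registration system only partly prevents selection by occupational physicians, because eligibility rests on the randomised physician's own diagnosis and first meeting

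*Protocol article*

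**What the plan says.** The Strengths and limitations section of the protocol article presents the route into the trial as protection against bias: participating workers are "selected by the registration system of the OHS and not by OPs; this may prevent selection bias from the individual OPs".

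The section Recruitment of participants defines who can be selected: "The workers eligible for this study are on sick leave due to CMD diagnosed by the OP, counselled by an OP participating in the study". Inclusion criterion 1 repeats that the diagnosis is the OP's, coded in the Dutch classification (CAS). Criterion 2 requires the worker to be "on current sick leave when selected from the registration system of the OHS after the first meeting with the OP".

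The Randomisation section makes the OP the randomised unit. The Blinding section names workers, companies and the analysing researcher as blinded; OPs are not named. On the guideline, the Intervention section says of step 1 that "A simplified classification of mental health problems is introduced in four categories", and that early involvement means "first assessment and start of counselling about 2 weeks after the worker reported sick". On the training, the article states: "This cycle of plan-do-check-act was repeated in each meeting for all the recommendations stated in the guideline". The Statistical analysis section would look for significant baseline differences between arms and take them into account if necessary.

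**The concern.** In a cluster trial, randomising clusters balances participants only if they are identified before allocation, or in a way that allocation cannot affect. Here the step that makes a worker identifiable is taken by the randomised person, after allocation. The registration system passes on what that person has recorded.

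There are two routes to a difference between arms:

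- **Diagnosis.** If trained and untrained OPs draw the line between CMD and other reasons for absence differently, the two arms contain different workers.
- **Timing.** Time to full return-to-work (RTW) is counted from the first day of absence, but a worker enters only if still absent after the first meeting. An arm that meets workers earlier captures more short absences.

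Either route can make RTW look faster or slower with no effect of care. What is at stake is how far a difference in the primary outcome can be attributed to guideline-based care.

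**Working it through.** **Step 1: trace the selection.**

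| Question | What the protocol article gives | Section |
|---|---|---|
| Who assigns the qualifying diagnosis? | The participating OP | Recruitment of participants |
| When is the worker selected? | After the first meeting with that OP, while still absent | Recruitment of participants |
| Is that OP already randomised? | The OP is the randomised unit, and intervention OPs are trained on the strength of that allocation | Randomisation; Content of the training |
| Does the OP know the arm? | Intervention OPs attend eight training meetings; OPs are not listed as blinded (an inference, not a statement) | Content of the training; Blinding |
| Does the intervention bear on the selecting step? | Step 1 is diagnosis and early first contact; the training works through all recommendations | Intervention; Content of the training |
| What does the registry add? | It takes eligible workers without the OP choosing among them | Recruitment of participants |

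The last row is a real protection. The rows above it show what it leaves open.

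**Step 2: the plan's own figures.** The point contests none of them. The pooled two-proportion formula (two-sided 0.05 assumed, 80% power) gives 89 per arm for 55% v 75% and 100 per arm for 75% v 90%. With 232/60 = 3.87 workers per OP and an ICC of 0.025, the design effect is 1 + 2.87 × 0.025 = 1.072. This gives 96 and 108 per arm, against 97 and 110 stated. Then 220/0.95 = 231.6, so 232, as stated. The sample size is not at fault.

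**Step 3: how sensitive is the comparison?** The documents give no coding rates, no severity mix and no meeting times, so every share below is an assumption. Take no true effect and let a fraction f of one arm consist of milder cases with RTW proportion r in place of the planned control value p. The spurious difference is d = f × (r − p).

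- 3 months, p = 55%, r = 75%: f = 10% gives 0.10 × 0.20 = 2 points; f = 30% gives 6 points.
- 3 months, p = 55%, r = 90%: f = 10% gives 0.10 × 0.35 = 3.5 points; f = 30% gives 10.5 points.
- 6 months, p = 75%, r = 90-95%: f = 10-30% gives 1.5 to 6 points.

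Against the planned 20 points at 3 months this is 10-52%; against the planned 15 points at 6 months, 10-40%. The sign follows the arm that holds the milder cases: positive for the intervention if they are there, equally negative if they are in the control arm.

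**Step 4: chance of a false finding in the favoured direction.** With 110 per arm and 220/60 workers per OP, the effective n is 110/1.0667 = 103.1. The chance is Φ[(d − 1.96·SE0)/SE1], where SE0 is the pooled and SE1 the unpooled standard error.

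- Smallest 3-month case, d = 0.02: (0.02 − 1.96 × 0.0691)/0.0691 = −1.67, about 5%.
- Largest 3-month case, d = 0.105: (0.105 − 1.96 × 0.0682)/0.0678 = −0.42, about 34%.
- 6 months: about 4-18%.

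The nominal value is 2.5%. The planned primary analysis is a survival analysis; proportions at fixed times stand in for it here.

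**The case against.** The case on the other side has substance.

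- **The sentence is hedged and partly true.** It says that selection bias may be prevented. OPs do not invite workers, and sick-leave data are taken from all eligible workers, so OPs cannot choose among those they have diagnosed. This stands: the statement is incomplete, not false.
- **The guideline is not new.** A reader might infer that intervention OPs learn a new classification that redefines who has CMD. The documents do not support that. The guideline dates from 2000, was revised in 2007 and was disseminated to Dutch OPs, and control OPs are expected to follow it. The contrast is training against low adherence. Inclusion is coded in CAS, not in the guideline's four categories. Moving a worker between stress-related complaints, depression and anxiety would probably leave eligibility unchanged; only a shift across the boundary of CMD matters, and nothing says that the training addresses it. This weakens the diagnosis route without closing it, and leaves the timing route untouched.
- **There are partial safeguards.** Questionnaire participants have their criteria checked by direct contact, and symptoms, burnout and history are measured at baseline. A milder arm could show there. But these cover only workers who consent. The symptom scales are completed after the first meeting with the OP, and the OP's diagnosis, also listed at baseline, is the very label in question.
- **Sensitivity analyses belong in fuller documents.** Agreed. Their absence from the article is not the point. The point rests on a property that the article claims and on an adjustment rule that it states.

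**Conclusion.** The point holds as a limit on a claimed strength. Selection through the registry protects against hand-picking among diagnosed workers. It does not protect against differential diagnosis, or against differential timing of the first meeting, by OPs who are already randomised and, in the intervention arm, aware of it. Adjustment only for baseline differences that turn out significant does not cover this.

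The documents show that case mix can differ by arm, not that it does, nor in which direction. The 2 to 10.5 points at 3 months describe sensitivity under assumed shares and are not an estimate of bias. A reader might infer that the design favours the intervention. That is not supported, since trained OPs could equally code fewer mild cases.

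The conclusion rests on one inference, that intervention OPs know their arm, which follows from attending the training. It calls for corrected wording and an inexpensive check; randomisation, intervention and sample size can stay as they are.

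**What to change.** 1. In Strengths and limitations, restate the sentence: the registry prevents OPs from choosing among diagnosed workers, but eligibility depends on the OP's diagnosis and first meeting. List identification after randomisation by OPs who are not blinded as a limitation.
2. Extract from the occupational health service's system, as aggregate figures per randomised OP, the number of first consultations, the number coded as CMD by CAS category, and the time from sick report to first consultation. Compare these by arm, allowing for clustering. Similar figures would be reassuring but would not prove equal case mix.
3. Adjust the model for time to full RTW for prespecified prognostic covariates that are already collected and that the OP does not assign, such as age, gender and sick leave in the previous year, instead of choosing them after baseline significance tests. The article does not say whether these are held for workers with registry data only; if not, adjustment reaches questionnaire participants alone.
4. If coding rate or timing differs by arm, interpret the primary effect with that caution.

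An analysis of all sick-listed workers should not be used to decide the matter. It would bring in physical illness, which the training does not target, so a true effect would shrink as well and shrinkage could not be read as case mix.

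The cost is a small extra registry extraction and a less favourable statement of the trial's strengths.

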### Impact of study results

This study will show whether guideline-based care in fact leads to faster and sustainable RTW. If the results are promising, this study will contribute to lower societal and financial costs and less negative consequences for workers with CMD. The training may also give OPs the tools to better handle the guideline in daily practice. Moreover, the approach applied in this study may be relevant for the implementation of this and other (occupational) guidelines in daily practice. Results of this study will become available in 2015.

## Abbreviations

CMD: Common mental disorders; RTW: Return-to-work; OP: Occupational physician; OHS: Occupational health service; NVAB: The Netherlands society of occupational medicine; CAS: Dutch classification of diseases; 4DSQ: Four dimensional symptoms questionnaire; UBOS: Utrechtse burnout scale; WAI: Work ability index; JCQ: Job content questionnaire; UCL: Utrecht coping list; RTW-SE: Return-to-work self-efficacy scale; RS-12: 12-Item remoralization scale; PSOHPQ: Patient satisfaction with occupational health professionals questionnaire
